#### Frailty

The Kihon checklist (KCL) [31] is used to assess frailty. The KCL is a self-report scale for frailty that has shown high validity in Japanese community-dwelling older adults. The KCL is commonly used in Japan, as municipalities across Japan have used it to determine high-risk populations to invite or evaluate intervention programs. The KCL includes 7 domains: daily life, physical strength, nutritional status, oral function, extent of house boundedness, cognitive function, and risk of depression. The total KCL scores and the occurrence and recovery of comprehensive or domain frailty will be assessed.

#### Social and Psychological Factors

Loneliness, well-being, health-related quality of life (HRQOL), and divergent thinking are introduced to evaluate the effects of conversational interventions on social and psychological aspects.

The University of California, Los Angeles Loneliness Scale-10 item version (UCLA-LS 10) [32] is used to assess loneliness. A total UCLA-LS score of 10 is calculated from the sum of each item (10-40 points). Higher scores on the UCLA-LS 10 indicate severe loneliness. The 5-item World Health Organization Well-Being Index [33] is introduced to evaluate well-being. The percentage score of WHO-5 is calculated (0-100 points) according to the manual. The Health Utilities Index Mark 3 [34] is used to assess HRQOL, and the multi-attribute utility score (–0.36 to 1.00) is calculated using the formula. Higher 5-item World Health Organization Well-Being Index and Health Utilities Index Mark 3 reflect better well-being and HRQOL. An item fluency test from the S-A creativity test [35], which is a divergent thinking assessment tool, is also introduced. While the S-A creativity test has 3 kinds of tasks that correspond to the 3 tasks of the Torrance test of creative thinking [36], including unusual use, product improvement, and just suppose, we only perform an unusual use task, which is an item fluency test to evaluate the flexibility of thought and divergent thinking, due to the balance between our study interest and time limitation. The 2 questions in the unusual use task ask participants to generate as many ideas as possible for the alternative uses of typical objects in unique ways in 5 minutes. The scoring of the S-A test is calculated using the formula by Tokyo Shinri Corporation.

#### Covariates

The covariates from the questionnaire include the following variables to describe participants’ demographics: age, sex, educational attainment, social isolation (the Lubben Social Network Scale-6) [37], and familiarity with devices such as smartphones, PCs, and email. Blood samples are also collected, with the measurement of blood-based biomarkers, including plasma neurofilament light chain (NfL), plasma tau, and tau in neuron-derived extracellular vesicles from plasma, which may reflect neuronal condition.

### Sample Size

We used G*power [38] to calculate the sample size, assuming the following conditions: 2-sided hypothesis test; medium effect size (f=0.25); 95% power; an analysis of variance model between groups over time; and 5% α level. Therefore, 65 participants are required, with a 20% dropout rate.

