## Methods

### Study Design

The PICMOA-2 trial is an open-label, 6-month RCT with 2 parallel groups, including 1 intervention group and 1 passive control group. The overall timeline of the procedure is shown as a SPIRIT flow in Table 1. The main and secondary outcomes will be assessed at baseline and after a 6-month intervention period.

**Table 1 table1:** Overall timeline of the procedure of the PICMOA-2 trial.

Time point				Enrollment		Allocation		Post allocation			Evaluation
				–t_1_		0		t_1_	t_2_		t_3_

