### Randomization and Blinding

Stratified block randomization, a block design (2, 4, and 6 block sizes) with a 1:1 allocation, was performed using the University Hospital Medical Information Network Internet Data and Information System for Clinical and Epidemiological Research Cloud version [39]. The participants were allocated to either the intervention or the control group. Sex (male or female) and MMSE scores (28 or higher and 27 or lower) at baseline were used for stratification. [name] is responsible for the randomization. As this study uses an open-label design, we aim to prevent potential assessment bias by blinding the assessors.

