### Statistical Analysis

This study evaluates the effects of the PICMOA-2 intervention on outcome measurements. Linear mixed models with random intercepts for outcome measurements will be used to estimate the intervention effects. Our model will include the group assignment factor, time factor, and group × time interaction term and evaluate the intervention effect from the interaction term. As a secondary aim, we will test whether the intervention effects varied with the covariates at baseline to examine the effective target attributes.

All analyses will be conducted using the R software (The R Foundation). Statistical significance will be set at *P*<.05.

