### Limitations

This study uses an open-label trial design. Although the assessors are blinded to avoid assessment bias, blinding the research staff and participants is not possible for such behavioral interventions. In addition, the sample size was designed with a minimum of 65 participants for feasibility considerations. Large-scale validation is required to examine the effectiveness of the intervention.

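### The 95% power quoted for a medium effect is power for a 1.0 SD between-arm difference in change; for 0.5 SD it is about 42% at the implied correlation

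*Protocol article*

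**What the plan says.** The Sample Size section of the protocol article names G*Power and lists a "2-sided hypothesis test" at 5% alpha, with these further conditions: "medium effect size (f=0.25); 95% power; an analysis of variance model between groups over time". It concludes that 65 participants are needed, allowing for 20% dropout. It gives neither the correlation between the two measurements nor the meaning of f = 0.25 as a difference in verbal fluency.

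Three other sections fix what is being powered. Study Design: "The main and secondary outcomes will be assessed at baseline and after a 6-month intervention period". Statistical Analysis: the mixed model will "evaluate the intervention effect from the interaction term". Randomization and Blinding: "a block design (2, 4, and 6 block sizes) with a 1:1 allocation". The tested quantity is therefore the between-arm difference in 6-month change, in a layout of two arms by two visits.

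The Limitations section gives a different basis for the number: "the sample size was designed with a minimum of 65 participants for feasibility considerations". The Results section reports 66 randomised.

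**The concern.** The label medium for f = 0.25 comes from comparing group means at one time. With two equal groups, f is half the standardised difference, so f = 0.25 is 0.5 SD. A reader will take the sentence as 95% power for roughly that effect. In a two-by-two interaction the same f stands for a different, larger difference, unless the software's effect-size option is changed.

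At stake is how a non-significant result is read. If 95% power for a medium effect were true, a null interaction would come close to ruling out a medium benefit of the intervention on verbal fluency. If the true power for that effect is near 40%, such a result says little about it.

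**Working it through.** **Inputs.** Two-sided alpha 0.05, power 0.95, f = 0.25, dropout 20%, stated N = 65 (Sample Size); k = 2 arms, 1:1 (Randomization and Blinding); m = 2 visits (Study Design); interaction test (Statistical Analysis); 66 randomised (Results). The correlation ρ between baseline and 6 months is not stated. It is inferred from N = 65 first, then varied.

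**Step 1: reproduce 65.** For the within-between interaction on G*Power's default scale, the noncentrality is λ = f² × N × m / (1 − ρ), with F on (1, N − 2) degrees of freedom.

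- ρ = 0.5, N = 54: λ = 0.0625 × 54 × 2 / 0.5 = 13.5; power 0.9501, and 54 is the smallest even N reaching 0.95. Then 54 × 1.2 = 64.8, rounded up to 65.
- ρ = 0.52: the smallest even N is 52 (power 0.9504), and 52 / 0.8 = 65.

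Two alternatives do not lead to 65, even before dropout:

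- between-groups factor at ρ = 0.5: N = 158;
- interaction with λ = f² × N (the other effect-size option): N = 210.

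Both routes to 65 use the default scale and a correlation close to 0.5.

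**Step 2: convert f into a difference in change.** Let D be the between-arm difference in change and SD the standard deviation at a single visit. In a two-by-two layout the four interaction effects are each ±D/4, so

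f = (D/4) / SD, that is, D = 4 × f × SD.

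f = 0.25 gives D = 1.0 SD, and D = 0.5 SD is f = 0.125. The correlation does not enter this conversion.

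Check: the noncentrality for comparing mean change between arms is D² × N / (8(1 − ρ)), with D in SD units. Setting this equal to f² × N × 2 / (1 − ρ) gives D² = 16f², so D = 4f, as above. Under the other option, f² × N = D² × N / (8(1 − ρ)); at ρ = 0.5 this gives D = 2f = 0.5 SD. That is the conventional medium difference, and it needs 210 completers.

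**Step 3: power for 0.5 SD.** With 65 × 0.8 = 52 completers and ρ = 0.5, λ = 0.015625 × 52 × 2 / 0.5 = 3.25 on (1, 50) df, and power is 0.424. Simulating change scores at 26 per arm gave 0.425. Across assumed correlations, with 52 completers and with all 66 randomised analysed:

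| ρ (assumed) | Power for 0.5 SD, N = 52 | Power for 0.5 SD, N = 66 |
|---|---|---|
| 0.3 | 32% | 39% |
| 0.5 | 42% | 52% |
| 0.6 | 51% | 61% |
| 0.7 | 63% | 73% |
| 0.8 | 80% | 89% |
| 0.9 | 98% | 99% |

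With 54 completers at ρ = 0.5 the figure is 44%; with 52 at ρ = 0.52 it is also 44%.

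**Step 4: what the design does detect.** At ρ = 0.5 with 52 completers, power for 1.0 SD is 94.2%. The difference detectable with 95% power is 1.02 SD at ρ = 0.5 and 0.79 SD at ρ = 0.7.

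**The case against.** The case on the other side has four parts.

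- **The number reproduces, and medium is the software's own label for f = 0.25.** True, and it explains how the sentence arose. But the label carries a meaning, about 0.5 SD, that does not transfer to this test, and the article gives no scale or correlation that would warn the reader.
- **The set-up and the correlation are inferred, and the true correlation of verbal fluency over 6 months may be higher.** This stands as a limit on the 42%: near 0.9, power for 0.5 SD would be about 98%. It does not rescue the printed claim. At ρ = 0.9, f = 0.25 would have needed only 14 participants before dropout, so the published 65 points to planning at about 0.5. The equality of f = 0.25 and 1.0 SD holds at any correlation.
- **52 completers may be pessimistic, since 66 were randomised.** Fair. Even with no dropout, power for 0.5 SD at ρ = 0.5 is 52%.
- **The Limitations section already discloses a small sample, and choosing the minimum for feasibility is compatible with a power calculation.** The two statements can be read together, and that section does call for larger validation. It leaves the 95% and the word medium unqualified, however.

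It is also true that recruitment has closed and nothing in the trial's conduct changes. That limits the remedy to wording; it does not make the statement correct.

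**Conclusion.** The concern holds. The printed 95% power belongs to a 1.0 SD between-arm difference in change, twice the difference that the word medium conveys. At the correlation implied by the sponsor's own N, power for 0.5 SD is 42% with 52 completers, 44% with 54, and 52% if all 66 are analysed.

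The 1.0 SD equivalence is algebraic, once the calculation is taken to be the default-scale interaction test, the only one tried that yields 65. The power figures further assume a two-sided 5% test of the difference in change, SD measured at a single visit, and the stated correlation. That correlation is not in the document and would have to be about 0.8 for 80% power at 0.5 SD with 52 completers. This should be corrected before results are reported, because it governs what a null finding can be said to exclude.

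**What to change.** Restate the power and enrol no one extra. In Sample Size, remove the word medium, say that f = 0.25 is on the default scale for the group-by-time interaction, give its equivalent in SD, and state the correlation actually used. If that was 0.5, suitable text is: *Assuming a correlation of 0.5 between baseline and 6 months and 52 completers, the trial has about 94% power for a between-arm difference in change of 1.0 SD and about 42% for 0.5 SD.* Show power for 0.5 SD over a range of correlations beside it, since 0.5 is a planning value.

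Make the Limitations section give the same basis for 65 as the Sample Size section. State there, and in the results report, that a non-significant interaction does not by itself exclude a 0.5 SD effect.

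The cost is a few sentences and a less favourable power statement. Outcomes, allocation and analysis stay as they are.

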### Randomization and Blinding

Stratified block randomization, a block design (2, 4, and 6 block sizes) with a 1:1 allocation, was performed using the University Hospital Medical Information Network Internet Data and Information System for Clinical and Epidemiological Research Cloud version [39]. The participants were allocated to either the intervention or the control group. Sex (male or female) and MMSE scores (28 or higher and 27 or lower) at baseline were used for stratification. [name] is responsible for the randomization. As this study uses an open-label design, we aim to prevent potential assessment bias by blinding the assessors.

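### Allocation is stratified by sex and MMSE category but the stated model has neither factor; its test is conservative only as far as these strata predict 6-month change

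*Protocol article*

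**What the plan says.** Randomization and Blinding describes "Stratified block randomization, a block design (2, 4, and 6 block sizes) with a 1:1 allocation", and then: "Sex (male or female) and MMSE scores (28 or higher and 27 or lower) at baseline were used for stratification". That makes four strata.

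Statistical Analysis fixes the model type, "Linear mixed models with random intercepts for outcome measurements will be used to estimate the intervention effects", and its terms: "Our model will include the group assignment factor, time factor, and group × time interaction term". It will "evaluate the intervention effect from the interaction term". Under Study Design there are two measurement occasions: "The main and secondary outcomes will be assessed at baseline and after a 6-month intervention period".

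No section puts the stratification factors into this model as adjustment terms. Sex is in the Covariates list, but that list is introduced as "variables to describe participants’ demographics: age, sex, educational attainment, social isolation" and so on, and MMSE is not in it. The only analytic use given to baseline covariates is the secondary aim of looking for effect modification.

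**The concern.** Stratified blocks keep the arms balanced on sex and MMSE category. If these factors predict the quantity being compared, the treatment contrast varies less between hypothetical repetitions of the trial than a model without them assumes. That model reports a standard error that is too large, and the precision which stratification was meant to secure is partly lost.

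The trial randomised 66 people, and the article's Limitations section calls its target of 65 a minimum chosen for feasibility, so avoidable loss of precision deserves a check. The question is whether the loss arises under this particular model, and how large it could be.

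**Working it through.** **The plan's own figure.** Sample Size gives 65, from f = 0.25, 95% power, two-sided 5% and 20% dropout. The article states no correlation between visits; 0.5 is assumed here. For the group × time test with 2 groups and 2 visits, λ = f²·N·2/(1 − ρ). At N = 54, λ = 0.0625 × 54 × 2 / 0.5 = 13.5 and power is 0.9501. Then 54 × 1.20 = 64.8, rounded up to 65. The figure reproduces and the present point does not alter it.

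**What the interaction estimates.** Write person i's score at visit t (0 or 1) as level + stratum effect + group and time terms + random intercept + error. With both visits observed, the group × time estimate is the difference between arms in mean change (6 months minus baseline). A stratum effect that is the same at both visits drops out of the change. One simulated data set with N = 54 and strong stratum effects on level gave:

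| Model | Estimate | SE |
|---|---|---|
| group × time only | 0.7205 | 0.3757 |
| plus sex and MMSE category as main effects | 0.7205 | 0.3757 |
| plus sex × time and MMSE category × time | 0.7264 | 0.3784 |

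Main effects change nothing. With about 20% of the 6-month values removed, the cancellation is no longer exact, but main effects still brought no gain (SE 0.429 without, 0.433 with).

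**If the strata predict change.** Let R² be the share of the variance of change that the strata explain. Under balance on the strata, the true SE is √(1 − R²) times the one the model reports. So:

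- SE ratio = 1/√(1 − R²)
- type I error = 2·[1 − Φ(1.96/√(1 − R²))]

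| R² (assumed) | √(1 − R²) | 1.96/√(1 − R²) | Type I error | SE too large by |
|---|---|---|---|---|
| 0% | 1.000 | 1.960 | 5.0% | 0% |
| 5% | 0.975 | 2.011 | 4.4% | 2.6% |
| 10% | 0.949 | 2.066 | 3.9% | 5.4% |
| 20% | 0.894 | 2.191 | 2.8% | 11.8% |

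**Simulation check.** Change scores were simulated under stratified blocks of 2, 4 and 6 with N = 54, assuming half of each sex and 60% in the upper MMSE stratum. Power is for a true difference of 1 SD of change. This matches the planned effect: with 27 per arm the noncentrality is 1/√(2/27) = √13.5.

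| R² | Empirical SD | Mean model SE | Type I, unadjusted | Type I, adjusted | Power, unadjusted / adjusted |
|---|---|---|---|---|---|
| 0% | 0.271 | 0.271 | 5.0% | 5.0% | 0.952 / 0.950 |
| 5% | 0.266 | 0.271 | 4.5% | 5.0% | 0.956 / 0.960 |
| 10% | 0.258 | 0.271 | 3.8% | 5.0% | 0.957 / 0.967 |
| 20% | 0.248 | 0.271 | 2.9% | 4.8% | 0.963 / 0.978 |

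The simulation agrees with the formula. At 20% the simulated SE excess is a little smaller (0.271/0.248 = 1.09), as expected when incomplete blocks leave some imbalance.

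**MMSE as an outcome.** MMSE is measured at both visits, and its stratum is cut from its own baseline. Assume bivariate normal scores with equal variances, a cut at the median and no treatment effect. The stratum then explains (1 − ρ)²·(2/π) / [2(1 − ρ)] = (1 − ρ)/π of the variance of change: about 16% at ρ = 0.5 and 10% at ρ = 0.7. Simulated type I error of the planned test with N = 66 was 3.4% and 4.0% respectively, against 5.0% and 5.1% with the strata adjusted. This is an illustration; the documents give neither the correlation nor the split.

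**The case against.** A reader might infer that, because the strata are omitted, the standard error is wrong in any case. The documents do not support that. With two visits and the effect read from group × time, each person is their own control. If the strata relate only to the level of verbal fluency, the model SE is correct (0.271 against an empirical 0.271). That MMSE category plausibly goes with fluency level is therefore not enough; it must go with change. Nothing in the article says that it does, in a sample already restricted to MMSE of 24 or more. This part of the objection stands, and it limits the point to its conditional form.

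The impact is also small and on the safe side: no scenario raised type I error, and at 10 to 20% of change variance the power gain was 1.0 to 1.5 percentage points, from about 96%. That stands too.

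Finally, the article is condensed, its wording does not say that no other terms will enter, and a fuller analysis plan may add the strata. That is possible, so the omission cannot be read as a decision to exclude them. But the article does more than stay silent. It commits to a specific model and gives baseline covariates other roles, description and effect modification. The model as stated does not match the allocation as stated, and the two can be aligned at little cost.

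**Conclusion.** The point holds in a limited form. The stated model leaves out both stratification factors, and its group × time test is conservative to the extent that sex and MMSE category predict 6-month change. Over an assumed range of 0 to 20% of change variance, type I error runs from 5.0% down to 2.8% and the SE is 0 to 11.8% too large. These figures assume complete two-visit data and near-balance within strata.

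For the primary outcome, verbal fluency, the documents give no basis for placing the trial within that range, and zero is compatible with them; the weight there is modest. For MMSE as an outcome some effect is plausible, because the stratum comes from the same baseline score. The omission does not threaten the validity of a positive result.

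**What to change.** State in the analysis plan that sex and MMSE stratum (28 or higher against 27 or lower) enter the effectiveness models in a form that reaches the treatment contrast:

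- In the planned mixed model, add sex × time and MMSE stratum × time with their main effects. Main effects alone leave the result unchanged when data are complete.
- If a baseline-adjusted model of the 6-month score is used instead, add both factors as covariates. That would be a change of model, so it should be a decision in its own right. For MMSE as the outcome, the baseline score and its category overlap; say whether both are kept.

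Both variables are already recorded. On the change scale the mixed-model option costs two error degrees of freedom (52 to 50 at N = 54). If the strata turn out not to predict change, the price is negligible: simulated power 0.950 against 0.952, and in the one complete example data set an SE of 0.3784 against 0.3757.

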### Statistical Analysis

This study evaluates the effects of the PICMOA-2 intervention on outcome measurements. Linear mixed models with random intercepts for outcome measurements will be used to estimate the intervention effects. Our model will include the group assignment factor, time factor, and group × time interaction term and evaluate the intervention effect from the interaction term. As a secondary aim, we will test whether the intervention effects varied with the covariates at baseline to examine the effective target attributes.

All analyses will be conducted using the R software (The R Foundation). Statistical significance will be set at *P*<.05.

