### Intervention

The intervention program is PICMOA-2, a web-based conversational intervention that uses a PC tablet at the participant’s home. Participants are instructed to take photos in their daily lives as much as possible according to the specific 12 themes during the 6-month intervention period and join conversational intervention based on PICMOA-2 once every 2 weeks for 6 months. Figure 2 describes the intervention structure of PICMOA-2. Participants are required to upload to the web system using a smartphone app that we originally developed before the intervention session, join the group conversational intervention session, and have a presentation and discussion about the photos that participants took during the session.

In the conversational session, each participant in a designated group of 4 gives a 1-minute speech about the 2 photos they took in their daily lives. Other participants then ask questions related to the photos, and the presenter answers the questions in the context of a natural conversation for 2 minutes for each photo. Research staff administer intervention using the PICMOA-2 system and support participants’ PC operations through remote access.

In the case of dropouts, substitutes are included in the group conversation to maintain the intensity of the intervention since different numbers of group members can lead to quantitative differences in the amount and duration of speaking, potentially impacting the effect sizes.

Smartphones for taking photos and PC tablets (Surface Go; Microsoft Corp) for conversational sessions with an internet connection were prepared for all participants.

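### The intervention is delivered in conversation groups of 4, but the stated model has no conversation-group term; if changes correlate within groups, the standard error of the effect is understated

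*Protocol article*

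**What the plan says.** The Study Design section describes two arms, "including 1 intervention group and 1 passive control group". Randomization and Blinding describes individual allocation: "Stratified block randomization, a block design (2, 4, and 6 block sizes) with a 1:1 allocation".

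Under Intervention, the treatment is a group conversation held once every 2 weeks for 6 months, in which "each participant in a designated group of 4 gives a 1-minute speech about the 2 photos they took in their daily lives" and the other members ask questions. For those who leave: "In the case of dropouts, substitutes are included in the group conversation to maintain the intensity of the intervention". The reason given is that "different numbers of group members can lead to quantitative differences in the amount and duration of speaking, potentially impacting the effect sizes".

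Under Statistical Analysis: "Linear mixed models with random intercepts for outcome measurements will be used to estimate the intervention effects". It continues: "Our model will include the group assignment factor, time factor, and group × time interaction term and evaluate the intervention effect from the interaction term". The group in that sentence is the trial arm, not the conversation group.

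Sample Size uses an analysis of variance between groups over time (two-sided, f = 0.25, 95% power, 5% alpha, 20% dropout) and arrives at 65. It mentions no ICC or design effect.

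**The concern.** This is a partially nested design: individuals are randomised, one arm is then treated in small groups, and no groups are described for the other arm. Members of a conversation group share partners, topics and group dynamics, so their changes may resemble one another. The stated model has nothing to carry that resemblance. A participant intercept removes stable differences between people. It does not remove a shared component of change, and the effect is read from change (arm × time).

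At stake is the precision claimed for verbal fluency, the primary outcome. If changes are positively correlated within groups, the interval is too narrow and P<.05 is reached too easily. The sample size relies on the same independence.

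**Working it through.** **Inputs from the article.** Groups of 4 in the intervention arm; passive control; two assessments (baseline and 6 months); 66 randomised 1:1; f = 0.25; two-sided alpha 0.05; 95% power; 20% dropout; required total 65.

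**Assumptions.** ICC of the 6-month change within a conversation group: 0 to 0.20. Layout: 8 stable groups of 4 (32 people) against 33 controls, because arm sizes are not reported and 33 is not a multiple of 4. Correlation between the two assessments: 0.5, for the power calculation only.

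**1. The plan's own figure.** For the group-by-time interaction, λ = f²·N·2/(1 − 0.5). At N = 54, λ = 0.0625 × 54 × 4 = 13.5, and the noncentral F with 1 and 52 degrees of freedom gives power 0.9501. Then 54 × 1.2 = 64.8, rounded up to 65. The stated total is therefore reproduced with independent participants and no clustering allowance. The implied difference on change is √(4 × 13.5/54) = 1.0 SD.

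**2. Standard error.** With two assessments and complete data, the arm × time test in a participant random-intercept model is the two-sample t-test on change. The design effect in the intervention arm is DE = 1 + (4 − 1)·ICC, and controls have none. The ratio of true to model standard error is √[(DE/32 + 1/33)/(1/32 + 1/33)]. For ICC 0.10 this is √[(1.30/32 + 1/33)/(1/32 + 1/33)] = √(0.07093/0.06155) = 1.07.

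**3. Type I error.** By formula it is 2·[1 − Φ(1.96/ratio)]. It was also simulated on change scores, with 100,000 to 200,000 trials per ICC in most runs. The ranges cover separate runs.

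| ICC | DE | SE ratio | Alpha, formula | Alpha, simulated |
|---|---|---|---|---|
| 0 | 1.00 | 1.00 | 5.0% | 4.9–5.0% |
| 0.02 | 1.06 | 1.02 | 5.4% | 5.3% |
| 0.05 | 1.15 | 1.04 | 5.9% | 5.8–5.9% |
| 0.10 | 1.30 | 1.07 | 6.8% | 6.7–6.8% |
| 0.20 | 1.60 | 1.14 | 8.6% | 8.6–8.8% |

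A Welch test of conversation-group mean changes against individual control changes stayed between 4.9% and 5.2% throughout.

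**4. Power once clustering is allowed for.** With equal arms the variance grows by (DE + 1)/2, so λ is divided by that factor. At 54 analysed and ICC 0.10, 13.5/1.15 = 11.74, giving 92.0%. At ICC 0.05 power is 93.5%, and at 0.20 it is 88.5%. The number needed for 95% power before dropout rises from 54 to 58, 62 and 70 at ICC 0.05, 0.10 and 0.20. These figures take no penalty for degrees of freedom. The group-mean test, with 7 groups of 4 against 26 controls, has about 90% power for 1.0 SD at ICC 0.10.

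**5. Can the group variance be estimated?** With 8 groups of 4, a one-way analysis of variance on change gives a zero or negative group variance in about 43% of trials at ICC 0.05 and 32% at 0.10. In those trials a fitted group random effect falls back to the model as now stated.

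**The case against.** The strongest reply is that nothing in the article shows that changes are correlated within groups. Sessions follow one staff-run format. On the described timings, four members with 1 to 2 minutes of speech and 2 × 2 minutes of questions each make 20 to 24 minutes a session, or 4 to 5 hours over about 12 sessions. The outcome is an individually performed test, scored by blinded assessors. None of this shows that the ICC is zero, but it gives no reason to favour 0.10 or 0.20 over smaller values. That part stands, and it limits the size of the point.

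Four stronger readings are tempting and should be resisted.

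- A reader might infer that the 5% error rate is simply not held. That needs a positive ICC, which the documents do not give.
- A reader might take the sentence "different numbers of group members can lead to quantitative differences in the amount and duration of speaking, potentially impacting the effect sizes" as an admission that outcomes cluster. It concerns only the number of members, and it explains why substitutes are used to keep that number constant.
- A reader might assume that the same four people stay together for 6 months. The article speaks of a designated group when describing the session and provides for substitutes; it does not say that membership is fixed. Changing membership would weaken the clustering and make a simple nested term approximate.
- A reader might say that the model has participant intercepts only. That is the natural reading, but the level is not named, and a fuller protocol or analysis plan could specify more.

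The last reservation does not dispose of the point. The article states its fixed effects and its random-effect type and takes the effect from the interaction. Even if the random intercepts included one for conversation group, an intercept constant over time would not help, because the groups form after randomisation and the correlation is in change.

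**Conclusion.** The point holds in conditional form. The delivery is in groups, while the stated analysis and sample size treat participants' changes as independent. Any positive within-group correlation of change understates the standard error of the intervention effect. Under the assumed layout, the excess over 5% is less than 1 percentage point at ICC 0.05, about 1.8 at 0.10 and close to 4 at 0.20. It is modest because the groups are small and only one arm is clustered. The algebra is certain; the ICC and the stability of the groups are not known. This should be fixed because the remedy is cheap, but the article does not show that error control fails in this trial.

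**What to change.** - **Primary model.** Keep the participant random intercept. Add a random effect for the originally assigned conversation group, multiplied by an indicator for the post-intervention observation in the intervention arm, so that baseline values and controls carry no group effect. Use Satterthwaite or Kenward-Roger degrees of freedom.
- **Companion analysis.** Because the group variance will often be estimated as zero, also report either conversation-group mean changes against individual control changes with unequal variances, or a sensitivity analysis with the ICC fixed over a range such as 0.02 to 0.10.
- **Membership.** State whether groups were stable. If membership changed materially between sessions, say so and call the nested term approximate.

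The cost is one term in the R model and one short extra analysis, using group membership that the study team should already hold. No further participants, visits or measurements are needed. The downside is a somewhat wider interval and the loss of power shown above: at ICC 0.10, from 95% to about 92% before any loss of degrees of freedom, or to about 90% with the group-mean test.
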